### Procedures

#### Primary data

Participants will be required to attend the Advanced Wellbeing Research Centre (AWRC) at Sheffield Hallam University on two separate occasions. The first visit will take place as soon as possible after diagnosis, during which participants will complete two questionnaires and four physical assessments. On arriving at the AWRC, participants will be greeted by a member of the research team and taken to the morphology lab where they will be seated in a neutral space with no sight of the equipment. The researcher will explain the study again and provide an opportunity to ask any questions before the participant provides their informed consent to participate.

Participants will then be asked to complete the following questionnaires: the EuroQol 5-Dimensions 5-Levels (EQ-5D-5L) to measure quality of life^29^ and the Patient Generated Subjective Global Assessment Short Form (PG-SGA-SF) to measure nutritional status.^30 31^ Next, participants will be asked to void their bladder, change into form-fitting, non-compressive clothing, and remove all jewellery to complete the four physical assessments: stature (Seca 264, Seca, Germany), body mass and body composition (proportions of fat and fat-free mass) using a BOD POD (Cosmed, Italy) and body size and shape (including waist, upper arm, and calf circumference) using the Size Stream SS20 3D body scanner (Size Stream, NC, USA). The second visit will take place within the 2 weeks prior to the participant having surgery, and the data collection for this visit will be the same as visit one, with the addition of another questionnaire to gather information on participants’ weight loss intentions, strategies and advice received; see online supplemental material 1.

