For the body composition and size measurements, participants will wear form-fitting, non-compressive clothing and a swim cap. Additionally, participants will be asked to refrain from eating or exercising within the 2 hours prior to the visit and to arrive in a normal state of hydration (ie, not drinking any more or less than they usually do). If a medical condition precludes a participant from fasting, they will be instructed to record what they eat before the session and to replicate this for the second session. The BOD POD estimates body composition using air displacement plethysmography, for which the procedure requires participants to be weighed on a set of calibrated scales and then sit inside the pod for approximately 3 min (two or three 45-second measurements). If participants are unwilling or unable to use the BOD POD, they will instead have their body composition measured using a set of bioelectrical impedance scales (TANITA MC-780MA-N S, TANITA Europe, Netherlands). The Size Stream SS20 procedures require participants to stand still inside the device for approximately 20 s (a single 6-second measurement).

For participants that are eligible and wish to volunteer to take part in the study but express that they are unable to attend the AWRC site, a member of the research team will conduct the two data collection sessions where the participant attends Active Together sessions. These sessions will not include BOD POD and Size Stream measurements and instead only include body mass and composition measurement performed using the bioelectrical impedance scales and questionnaires. These participants will be included in the study to maximise recruitment and the amount of data collected, as well as attenuating the bias of the data towards participants that are more mobile/have access to transport/live closer to the AWRC.

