Separate linear regression models will be created to investigate the amount of variation in self-reported and clinical outcomes which are explained by preoperative changes in patient body measures. Then, multivariate regression models will be created which combine patient outcome measures that contribute significantly to the estimation of clinical outcomes. Ordinal logistic regression models will also be used to explore the relationship between patient outcome measures and ordinal clinical outcome variables, such as surgical complications (Clavien-Dindo classification) and the surgical approach used. Where the distribution of data indicates it would be appropriate (ie, for non-linear relationships between predictor and outcome variables), other regression approaches such as restricted cubic splines or generalised additive models will be used. Regression analyses are appropriate as this is exploratory research, and this approach allows the observation of relationships between all variables. The regression models will all be adjusted for the variability in time between the assessment points, tumour group and pretreatment therapies where these are shown to reduce residual variance and not introduce collinearity to the model. Any outliers will be investigated to ensure that they are legitimate observations; only implausible data will be removed.

Multiple regression models will be assessed for multicollinearity between input variables using variance inflation factor and tolerance collinearity statistics and for independence of errors using the Durbin-Watson test statistic. If the largest variance inflation factor value is >10, or tolerance values are below 0.2 this could indicate potential issues in the model associated with multicollinearity. Also, if Durbin-Watson values differed significantly from two this would suggest dependence of errors between input variables in the model. Additionally, regression assumptions (eg, homoscedasticity, normally distributed errors) will be checked via diagnostic plots, and transformations of variables will be used if assumptions are not met.

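### Body composition comes from two devices, with no explicit one-device rule for on-site participants and no device term among the listed adjusters, so device difference can enter composition levels and, through any switching, composition change

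*Protocol article*

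**What the plan says.** All of this is in the protocol article.

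- **Default device (Primary data).** Body composition is measured by air displacement in the BOD POD.
- **On-site fallback (Primary data).** Someone on site who declines the BOD POD or cannot use it is given a substitute: "they will instead have their body composition measured using a set of bioelectrical impedance scales".
- **Off-site participants (Primary data).** "a member of the research team will conduct the two data collection sessions where the participant attends Active Together sessions". Neither the BOD POD nor the body scanner is used there, and what remains is described as sessions that "instead only include body mass and composition measurement performed using the bioelectrical impedance scales and questionnaires". Body size and shape have no substitute device, so they are simply absent for this group.
- **Reason for off-site inclusion (Primary data).** One stated purpose is "attenuating the bias of the data towards participants that are more mobile"; transport and distance from the centre are named as well.
- **Visit 2 (Primary data).** "the data collection for this visit will be the same as visit one", with one questionnaire added. The device is not mentioned.
- **Adjustment (Statistics and analysis).** "The regression models will all be adjusted for the variability in time between the assessment points, tumour group and pretreatment therapies", each only where it reduces residual variance and does not bring in collinearity. Device is not listed. The same section says that directed acyclic graphs determine the adjustment variables.
- **Use of composition (Statistics and analysis).** Preoperative change in composition is an exposure in the regressions. Body composition, with no mention of change, also appears in the list of variables to be correlated with clinical outcomes.

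**The concern.** Air displacement and impedance are different methods, and nothing in the article says that their readings are interchangeable. Pooling them as one variable has two possible consequences.

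1. **Change.** If a participant has one device at visit 1 and the other at visit 2, the change score contains the difference between methods as well as any real change.
2. **Levels.** If composition at one time point is correlated with an outcome, any offset between devices is part of the variable. Off-site participants all have impedance, and the article describes the people it reaches this way as less mobile or with poorer access. Device can therefore stand in for fitness and recovery, which are among the outcomes.

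Composition is where this study goes beyond weight alone. The Introduction argues that loss of fat may help while loss of muscle is likely to harm. An artefact here would fall on the analyses meant to separate the two.

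**Working it through.** **1. The plan's own figures.** Regression: f² = 0.15, 6 predictors, alpha 0.05, power 0.80. The omnibus noncentral F test with 6 and N − 7 degrees of freedom and λ = 0.15N gives N = 98 (power 0.804), as stated; at the planned N = 100, power is 0.813. Correlation: rho = 0.3, two-tailed. The Fisher z formula gives 84.9 and a t-based variant gives 82, in line with the stated 84. Neither figure is disputed.

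**2. Who can have a mixed-device change score.**

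| Group | Visit 1 | Visit 2 | Mixed pair possible? |
|---|---|---|---|
| Off site | impedance | impedance | No: both sessions are off site |
| On site, BOD POD at both visits | BOD POD | BOD POD | No |
| On site, fallback at both visits | impedance | impedance | No |
| On site, fallback at one visit only | one device | the other | Yes: no explicit rule excludes it |

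The article does give an explicit repeat rule for food intake in participants who cannot fast, but none for the device.

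**3. Same device at both visits.** If impedance reads true value + c, the change is (x₂ + c) − (x₁ + c) = x₂ − x₁, so a constant offset cancels. In 4,000 simulated datasets of 100 per setting, with no true association, impedance shares of 10-40% and outcomes differing by 0.5 SD between device groups (all assumed), the false-positive rate was 4-5% without a device term.

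**4. Switching (assumed inputs).** The documents give no switching rate and no between-device bias. Assume a share s = 10-20% switches, mean device difference b = 2-6 kg of fat, extra SD e = 2-3 kg in switchers, SD of true change 3 kg, and 1 kg of ordinary same-device error.

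- V = 3² + 1² = 10; A = s·e² + s(1 − s)·b²; multiplier on the correlation = √(V/(V + A)).
- Low end: A = 0.1×4 + 0.09×4 = 0.76; multiplier 0.964; 0.30 becomes 0.29.
- High end: A = 0.2×9 + 0.16×36 = 7.56; multiplier 0.755; 0.30 becomes 0.23.
- Power at N = 100, Φ(√97·atanh r − 1.96): 0.86 at r = 0.30, 0.83 at the low end and 0.62 at the high end.

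**5. Pooled levels (assumed inputs).** Let p be the impedance share, d the device offset and g the outcome difference between device groups, both in SD. With no true association, the induced correlation is p(1 − p)dg / √[(1 + p(1 − p)d²)(1 + p(1 − p)g²)].

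- p = 0.2, d = g = 0.5: 0.04/1.04 = 0.038; false-positive rate at N = 100 about 7%.
- p = 0.4, d = g = 0.8: 0.1536/1.1536 = 0.133; about 26%.

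Simulation over the same grid gave 6-27% without a device term and about 5% with one.

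**6. Cost of a device term.** As a seventh predictor, omnibus power at N = 100 is 0.785 against 0.813, and the N for 80% power is 103 against 98. The six predictors are not listed, so device could also be one of them. A test of a single coefficient at f² = 0.15 needs N = 55 with either 6 or 7 predictors.

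**The case against.** The strongest reply has four parts.

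- **The device is largely fixed already.** Off-site participants have impedance at both sessions, and visit 2 is described as repeating visit 1. This stands for the off-site group. For on-site participants the general statement does not settle what happens when someone who used the BOD POD at diagnosis cannot or will not use it before surgery. No sentence says that the fallback is chosen afresh at each visit or that visit 2 may move off site, so frequent switching cannot be inferred.
- **A constant offset cancels in change.** Correct, as step 3 shows. A reader might infer that device difference contaminates the main exposure in a way that tracks mobility. The documents do not support that: the group they link to mobility has its device fixed, and possible switching is confined to on-site attendees, for whom no such link is stated. The two mechanisms concern different people and different variables. The 6-27% false-positive range belongs to levels, not to change.
- **The graphs may deal with it.** They determine adjustment, and the Figure 2 caption shows that well-being, including physical fitness, is in the graph. Adjusting for fitness could remove part of the outcome difference assumed in step 5. Figure 2 and the supplementary graphs are not available here, so a device node cannot be ruled out. The adjusters named in the text do not include one.
- **This is detail for a fuller plan, in an exploratory study.** Partly so. But the article names its adjusters and the fallback device, and followed as written these pool two methods. A mixed-device pair cannot be repaired later.

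It is also tempting to set a 3-point difference in percent fat (3 kg at 100 kg) beside the 3.2% weight loss in the Introduction. That figure is total body weight from a cited study, and such an artefact would affect switchers only.

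**Conclusion.** The point holds, at moderate severity and for composition analyses only. Two methods are pooled, no explicit rule keeps an on-site participant on one device, and device is missing from the listed adjusters. Device difference can reach composition change only through on-site switchers or through device-specific error in change that is not a constant offset. It reaches composition levels directly, and there it is tied to mobility and access. Body mass change, which the article counts among its key outcomes, is not affected.

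The size is not known. The fall from 0.30 to 0.29-0.23 rests on an assumed 10-20% switching rate and assumed device differences; its low end is negligible. The 7% and 26% for levels likewise rest on assumed shares, offsets and outcome differences, and the upper figure needs all three at their highest values. A reader might conclude that the composition results are invalid as planned; the documents do not support that.

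**What to change.** 1. Record the device at each visit, and state that each participant keeps one device across visits where possible.
2. Compute composition change only from same-device pairs. Treat a mixed-device change as missing and pass it to the missing-data procedure already described.
3. Include device in every composition model as a forced covariate, exempt from the condition that an adjuster must reduce residual variance. In composition-level correlations, stratify by device or use partial correlations given device.
4. Add a sensitivity analysis restricted to participants measured by BOD POD at both visits.

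**Cost.** One degree of freedom: omnibus power at N = 100 goes from about 0.81 to 0.785 if device is a seventh predictor. Switchers lose composition change. At the assumed 10-20% switching, 100 pairs become 90-80, and by the formula in step 4 power for r = 0.30 is 0.82-0.78. Against the 0.83-0.62 from keeping mixed pairs, the gain is in validity throughout and in power only when the device difference is large. Switchers may differ from others, so their missing change should not be assumed to be completely at random.

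An extra impedance reading in all attendees at the research centre would give a like-for-like pair for everyone. It is optional and not needed for this fix.

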#### Secondary data

In addition to the outcomes detailed above that will be gathered by the research team, data will be collected as part of the participants’ usual care from two other sources: from their NHS records for surgical information, hospital length of stay, readmissions and 1-year survival, and from the Active Together service for physical fitness and questionnaire assessments (table 1). These outcomes will be measured at the time points outlined in figure 1. The physical fitness outcomes from Active Together will be collected by members of the Active Together team, with the procedures used to collect this data provided in online supplemental material 2.

**Table 1 T1:** Data collected by the hospital and Active Together.

Hospital data	Active Together outcomes	
Surgical outcomes	Physical fitness	Questionnaires
Clavien-Dindo classification of postoperative surgical complications	6-minute walk test distance (m)	Patient-Generated Subjective Global Assessment Short Form
Type of surgical complications	60-second sit-to-stand repetitions	Quality of life: EuroQol 5-Dimensions 5-Levels
Length of operation time	2-minute step test repetitions	Fatigue: Functional Assessment of Chronic Illness Therapy-Fatigue
Surgical approach	Handgrip strength (kg)	Anxiety: General Anxiety Disorder 7
Length of critical care stay post-surgery	Blood pressure (mm Hg)	Depression: Patient Health Questionnaire 9
Length of hospital stay post-surgery	Physical activity level (exercise vital signs)	Self-Efficacy for Exercise Scale
Readmissions within 30 and 90 days (and reason for this)		
1-year survival		
Treatment pathway		

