**Ethics and dissemination:**

Ethical approval has been obtained from the Health Research Authority (Integrated Research Application System project ID 361634; Research Ethics Comittee reference 26/YH/0019). Written informed consent will be obtained from all participants. Data will be processed in accordance with General Data Protection Regulations and the Data Protection Act 2018. Findings will be disseminated via peer-reviewed publications, conference presentations and patient and public involvement activities.

STRENGTHS AND LIMITATIONS OF THIS STUDYThe observational nature of the study provides an ecologically valid insight into patient outcomes in an evidence-based cancer prehabilitation service.Longitudinal assessment of body mass and composition, surgical outcomes, physical fitness, nutritional status and quality of life allow investigation of the relationships between the changes in each metric across the perioperative period.The observational nature of the study precludes the ability to draw causal inferences.The potential heterogeneity of participant characteristics and treatment pathway may confound the associations reported; however, these will be accounted for statistically where possible.

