## Introduction

 Gastrointestinal (GI) cancers are a leading cause of global morbidity and mortality^1 2^ and induce significant costs to health services.^3^ Surgical intervention (eg, resection) is a primary treatment for GI cancers.^4^ However, surgery carries the risk of complications, risks which are increased for individuals with obesity.^5 6^ Consequently, patients with obesity are advised to lose weight prior to surgery.^7^ Previous research has shown that weight loss is feasible in a pre-surgery context for cancer patients^8^ and does not lead to increases in length of stay or postoperative complications.^9 10^ Indeed, a recent randomised controlled trial feasibility study investigating intentional pre-surgery weight loss in colorectal cancer patients reported no difference in complications between the weight loss and usual care group, and that those who lost more than 3.2% of their body weight had a 50% reduction in surgical complications.^11^

However, although weight loss may make the surgical procedure easier for surgeons to perform and/or reduce the risk of surgical complications, the effects of weight loss must be viewed within the context of the whole cancer patient journey. Indeed, greater preoperative weight loss is associated with worse long-term outcomes such as mortality and disease recurrence in upper GI and colorectal patients.^1012^,^14^ A possible explanation is that weight loss prior to surgery, particularly rapid weight loss, may result in the reduction of not only fat mass but also muscle mass, which is associated with increased mortality^15^ and is linked to metabolic disease.^16^ Additionally, low muscle mass has been associated with post-operative complications in cancer patients undergoing gastric surgery.^17^ Estimates suggest that one in two people with cancer will experience cachexia,^18 19^ which causes approximately 20–30% of all deaths in cancer patients.^20 21^ Consequently, interventions with the potential to exacerbate cachexia require thorough evaluation prior to adoption.

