### Statistics and analysis

Directed acyclic graphs have been created for the outcome measures in this study to identify confounding factors and determine which variables to adjust for during analysis. Figure 2 shows the causal pathway and potential confounders for investigating the effect of body composition changes on surgical outcomes. Online supplemental material 3 includes directed acyclic graphs for preoperative well-being, post-treatment well-being and 1-year survival. All quantitative data will be treated as continuous data, excluding Clavien-Dindo classification of postoperative surgical complications (ordinal) and the surgical approach, type of surgical complications and treatment pathway (nominal).

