**Figure 2 F2:**
[figure not shown]
Directed acyclic graph for investigating the effect of body composition changes on surgical outcomes. Baseline and preoperative well-being include nutritional status, psychological well-being and physical fitness.

Pearson (or Spearman, depending on the distribution of the data) correlation coefficients will be calculated to explore associations between outcome measures (eg, body weight, size and shape, body composition, body mass change, PG-SGA-SF, EQ-5D-5L, etc) and clinical outcomes (eg, surgical complications, length of stay, number of emergency readmissions and length of operating time). P values <0.05 will be considered statistically significant. Linear and multivariate regression models will then be used to investigate the strength of associations between preoperative changes in patient body measures (eg, body weight and composition), self-reported outcomes (ie, questionnaire data) and clinical outcomes. Additionally, exploratory analyses comparing outcomes between groups of participants (eg, those that lose weight vs those that do not) will be completed, with groups created using thresholds used in the previous literature^10^ and/or data-driven approaches such as a median split^11^ or optimal cut-point determination^32^.

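### Tumour stage and comorbidity are in neither the listed hospital data nor the named adjusters, and the rule for keeping adjusters is not a confounding rule

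*Protocol article*

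**What the plan says.** Under Secondary data, the protocol article describes the hospital extraction as information "from their NHS records for surgical information, hospital length of stay, readmissions and 1-year survival". Table 1, headed "Data collected by the hospital and Active Together", gives nine hospital items: complication grade, complication type, operating time, approach, critical care stay, hospital stay, readmissions, 1-year survival and treatment pathway.

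Under Statistics and analysis, directed acyclic graphs were drawn "to identify confounding factors and determine which variables to adjust for during analysis". The graph for surgical outcomes is Figure 2; the one for 1-year survival is in supplemental material 3. Of Figure 2 only the caption can be read, which says: "Baseline and preoperative well-being include nutritional status, psychological well-being and physical fitness".

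The same section then states: "The regression models will all be adjusted for the variability in time between the assessment points, tumour group and pretreatment therapies", with the condition "where these are shown to reduce residual variance and not introduce collinearity to the model".

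The strengths and limitations box rules out causal conclusions. It concedes that differences between participants and treatment pathways may confound the results and adds: "however, these will be accounted for statistically where possible".

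**The concern.** The Introduction makes disease severity an obvious common cause. It reports that "one in two people with cancer will experience cachexia", attributes roughly 20–30% of cancer deaths to cachexia, and links greater preoperative weight loss to later mortality and recurrence. A patient with more advanced disease or more comorbidity may lose more weight and muscle before surgery and also do worse afterwards, without the one causing the other.

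If severity is not measured and adjusted for, an association of body change with complications or 1-year survival cannot be separated from it. This matters because the Introduction wants the results to inform guidance for dietitians and exercise professionals.

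The retention rule adds a second problem. Whether a covariate lowers residual variance is a question of precision. A confounder matters because it is related to both exposure and outcome, so one tied closely to body change and modestly to outcome can bias the coefficient while barely improving fit. The rule could then drop it.

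**Working it through.** **1. Where each adjuster's data come from**

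| Variable | Named adjuster | Source stated |
|---|---|---|
| Time between assessments | yes | visit and assessment dates |
| Tumour group | yes | cancer type checked at screening (Participants) |
| Pretreatment therapies | yes | treatment pathway (Table 1) |
| Tumour stage | no | none |
| Comorbidity or anaesthetic risk | no | none |

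Table 1 is mainly a list of outcomes, but treatment pathway is a covariate, so it is not purely one.

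**2. The plan's own sample size**

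Inputs from Statistics and analysis: f²=0.15, α=0.05, power 0.8, 6 predictors, stated N=98. For the omnibus F test with u predictors, λ=f²N, the degrees of freedom are u and N−u−1, and power is the probability that a noncentral F exceeds the 95th centile of the central F.

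- u=6: the smallest N with 80% power is 98 (λ=0.15×98=14.7). The stated figure is reproduced. Power at N=100 is 81.4%.

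**3. Cost of adding stage and comorbidity to the six**

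| Predictors | N for 80% omnibus power | Omnibus power at N=100 |
|---|---|---|
| 6 | 98 | 81.4% |
| 8 (one df each) | 109 | 75.8% |
| 10 (stage in several categories) | 118 | 70.7% |

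For one body-change coefficient with partial f²=0.15 (1 numerator df, λ=0.15×100=15), N=55 suffices with 6 or 8 predictors, and power at N=100 is about 97%. The article does not name its six predictors. If stage and comorbidity are already among them, there is no cost.

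**4. Illustration of the possible bias (assumed inputs, unadjusted correlations)**

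Assume that a share p=0.4 has advanced stage, that body change has no true effect, and that stage shifts both body change and outcome by d SD. Then r = p(1−p)d² / (1+p(1−p)d²), with p(1−p)=0.24. The rejection probability uses Fisher's z with √(N−3)=√97.

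- d=0.5: r=0.06/1.06=0.06; P(p<0.05)=9%
- d=0.8: r=0.1536/1.1536=0.13; 26%
- d=1.0: r=0.24/1.24=0.19; 49%

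The nominal rate is 5%.

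A second form treats severity as continuous, correlated equally with body change and outcome, so that the induced r is the product of the two correlations. Correlations of 0.3, 0.4, 0.5 and 0.55 give r=0.09, 0.16, 0.25 and 0.30, with rejection in 14%, 36%, 71% and 87%. Severity would have to correlate at about 0.55 with both before it alone produced the rho=0.3 on which the correlation sample size rests.

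**The case against.** A reader might infer that stage and comorbidity will not be collected and so cannot be adjusted for. The article does not establish that. The graphs are said to decide adjustment and may contain both variables; a figure or supplement that cannot be read here is not a fault in the plan. Nor is Table 1 exhaustive. Tumour group, age and the routine pre-surgery weight are all used or checked elsewhere in the article and are absent from it. A condensed article can leave a covariate list to the full protocol. These points stand.

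A reader might also infer that the study will present confounded associations as effects. That is too strong. The limitations rule out causal conclusions and admit confounding. The word effect is used of the graph's purpose, not of planned results.

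Several design features also reduce the problem:

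- entry is limited to patients planned for curative surgery, which narrows the range of severity;
- treatment pathway, tumour group and pretreatment therapies carry some information on stage;
- baseline nutrition, psychological well-being and fitness are partial markers of severity;
- the visit 2 questionnaire allows intentional, unintentional and no weight loss to be compared, which bears directly on cachexia.

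None of these measures stage or comorbidity, so control remains partial.

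What the objection does not remove is the inconsistency in the text. If the graphs contain stage and comorbidity, the stated adjusters and listed data do not match them. If they do not, plausible common causes have been left out. In either case a residual-variance test is the wrong way to decide whether a confounder stays.

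**Conclusion.** The point holds in a limited form. The listed hospital data and named adjusters omit stage and comorbidity, and retention depends on a criterion unrelated to confounding. If the plan is followed as stated, disease severity remains a rival explanation for any association of weight or fat-free-mass loss with complications or 1-year survival.

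The size of the bias cannot be derived from the article. The 9% to 49% range depends on an assumed 40% with advanced stage and assumed shifts of 0.5 to 1.0 SD. It applies to unadjusted correlations and says nothing about the regressions once partial proxies are included. At the mild end the excess over 5% is small.

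This should be corrected because the remedy is specific and inexpensive. It does not invalidate the study.

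**What to change.** - Add clinical stage at diagnosis and one comorbidity or anaesthetic-risk measure to the hospital extraction in Table 1. This assumes that the surgical record already holds them, which the article does not say.
- Include both as pre-specified confounders in the surgical-outcome and 1-year-survival models, whether or not they reduce residual variance. Where events are few, use penalised estimation and keep them in.
- State the adjustment set derived from the graphs for each outcome, and rewrite the regression paragraph and Table 1 to agree with it.
- Drop the residual-variance condition for any variable classed as a confounder.

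The cost is a few fields from records already being accessed, a data-dictionary change, and Health Research Authority approval if an approved document has to be amended. Early extraction is preferable, since no further record data are taken after a post-surgery withdrawal.

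Statistically, if the two variables come on top of the planned six (8 predictors), omnibus power at N=100 falls from 81.4% to about 76%, and 80% would need N=109. The plan should acknowledge this. Power for a single body-change coefficient at partial f²=0.15 stays about 97%, so the sample size does not prevent the adjustment.
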